### *Visit 2 for discussion of result (Optional CRC visit)*

Results from screening visits will be discussed- participant have the option of attending CRC to have results discussed in person and may choose to have results discussed over the phone.

Subjects not eligible for further participation in study will be referred for appropriate care

Subjects eligible to proceed to randomization will have urine pregnancy test done

### *Randomization visit*

The following data will be collected at randomization visit:

- Record of urine pregnancy test results
- Record of concomitant medications- ensure patient has not been started on vitamin D in the interim between screening and randomization assessment
- Physical activity are quantified using the validated Paffenbarger Physical Activity Questionnaire^30^

This is a double blinded study. Subjects eligible to proceed with study will be randomly allocated to either Vitamin D3 4000iu/ day Placebo in a 1:1 ratio. Randomization to either treatment arm will be done through central independent randomization with help of CRC hospital Pulau Pinang.

### *8.1.4 .Visit 4*

Visit 4 occur at 8 (+/-1) weeks post randomization -

The investigator will perform the following procedures:

- - Record any change of dose administration of study treatment
  - Record any AE or SAE
  - Dispense study treatment
  - Measure serum calcium, phosphate and albumin level

### *8.1.5.Visit 5*

Visit 5 occur at 16 (+/-1) weeks post randomization -

The investigator will perform the following procedures:

- - Record any change of dose administration of study treatment
  - Record any AE or SAE
  - Dispense study treatment

### *8.1.5.Visit 6*

This is the final visit- all subjects will attend fasting and have

- Repeat clinical examination- including
  - Blood pressure measurement- average of 3 readings (sitting)
  - BMI
  - Waist: Hip ratio
- Repeat 75g Oral Glucose tolerance test—with measurement for
  - glucose and Insulin at time 0,60,90 and 120 minutes
- Repeat Blood tests for plasma 25(OH) D, calcium, phosphate, albumin, Fasting lipid profile, HsCRP and Urinary microalbumin creatinine ratio.

Study visits schedule and procedures are summarised in the table below:

|  | **Screening** | **Assessment of results (optional CRC visit)** | **randomization** | **Treatment** | | **End** | |
| --- | --- | --- | --- | --- | --- | --- | --- |
| **Visit** | **1** | **2** | **3** | **4** | **5** |  | **6** |
| **Timeline** | **-2 wks** | **-1 wk** | **0 +/-1 wks** | **8 +/-1 wks** | **16 +/-1 wks** |  | **24**  **wks** |
| **Procedures** |  |  |  |  |  |  |  |
| Check eligibility | X | X | X |  |  |  |  |
|  |  |  |  |  |  |  |  |
| Informed consent | X |  |  |  |  |  |  |
| Randomisation |  |  | X |  |  |  |  |
| Patient demographics & medical history | X |  |  |  |  |  |  |
| Clinical examination- incl BP/ WHI/BMI  Paffenburger physical activity score | X |  | X |  |  |  | X |
| Lab test:  UE/ Creatinine/ LFT  Calcium, phosphate and albumin  Fasting lipid profile  HsCRP  Urinary Microalbumin Creatinine Ratio  2 hour 75g OGTT with glucose and insulin | X  X  X  X  X  X |  |  | X |  |  | X  X  X  X |
| Plasma 25(OH) D | X |  |  |  |  |  | X |
| Urine Pregnancy test |  | X |  |  |  |  |  |
|  |  |  |  |  |  |  |  |
| Report AE and SAE |  |  | X | X | X |  | X |
| Dispense study treatment |  |  | X | X | X |  | X |
| Complete relevant section of CRF | X |  | X | X | X |  | X |

## Criteria for stopping subject treatment

Subjects can withdraw consent from study at any time point without compromising care

Subjects who became pregnant during duration of study will be withdrawn and referred for follow up as per local practice

Subjects who are deemed inappropriate for further continuation at discretion of study co-ordinator will be withdrawn from study and reason documented

## Dropouts and withdrawals

50% drop out rate is included in statistical calculation

Reasons for drop outs will be documented as far as possible

## Sample handling and analysis

## Collection

105 ml of blood will be drawn for through the 6 months study duration- consisting of:

50 ml of blood will be drawn at screening visit (wk -2) for –

UE, creatinine, LF, Calcium and phosphate, fasting lipid profile, HsCRP (5ml)

plasma 25(OH) vit D ( 5ml)

OGTT at time 0, 60,90 and 120 min for glucose ( 20ml) and insulin ( 20ml)

5 ml of blood will be drawn at visit 4 (wk 8) for-

Calcium, phosphate and albumin (5 ml)

50ml of blood will be drawn at study completion ( wk 24) for-

Calcium, phosphate and albumin, fasting lipid profile, HsCRP (5ml)

plasma vit D ( 5ml),

OGTT at time 0, 60,90 and 120 min for glucose (20ml) and insulin ( 20ml)

### Shipment of samples

- Plasma UE, creatinine, LFT, Calcium, phosphate, Lipid profile and glucose will be send for immediate analysis in biochemistry laboratory in Penang General Hospital
- Plasma 25(OH)D level will be send for immediate analysis in biochemistry lab in Island hospital, Penang
- HsCRP and Insulin during 75g OGTT will be collected in EDTA bottle, spinned down and sample stored in -20°C fridge. Samples will be shipped to IMR lab for analysis when sufficient samples are accumulated

9 STUDY QUALITY ASSURANCE AND DATA MANAGEMENT

## 9.1 Study Quality Assurance

### *Pre-study*

- SOPs will be prepared for CRC PMC
- The investigators will review the protocol and study procedures with study stuff
- All investigators and staff are GCP trained

# 9.2 DATA MANAGEMENT

Consent form and Case report forms will be filed in a locked filing cabinet in the study coordinator’s locked office.

Data will be double-entered by two research assistants to minimize data entry errors. All electronic data will be stored in a password-protected database. Only individuals listed on the staff form for this study will have access to the database.

# 10 STATISTICAL METHODS

## 10.1 Sample size and power considerations

Using AUC insulin:
By using nQuery Advisor version 6.01, from paper written by Gedik et al (Effects of vitamin D deficiency and repletion on insulin and glucagon secretion in man ^)16^, a sample size of 4 will have 95% power to detect a difference in means of -4.610 (e.g. the First condition mean, µ1, of 9.090 and a Second condition mean, µ2, of 13.700), assuming a standard deviation of differences of 1.200, with a 0.050 two-sided significance level. By adding 40% dropped out patient in case of lost to follow up unplanned pregnancy, the total sample for 2 arms (placebo and treatment group) treatments is 11 patients.

Using HOMA-IR:
By using nQuery Advisor version 6.01, from paper written by Von Hurst et al (Vitamin D supplementation reduces insulin resistance in South Asian women living in New Zealand who are insulin resistant and vitamin D deficient - a randomised, placebo-controlled trial )^31^, a sample size of 9 will have 95% power to detect a difference in means of 0.700 (e.g. the differences between Group 1 mean, µ1, of 0.800 and a Group 2 mean, µ2, of 0.100), assuming that the common standard deviation is 0.384, with a 0.050 two-sided significance level. By adding 40% dropped out patient in case of lost to follow up or unplanned pregnnacy, the total sample for 2 arms (placebo and treatment group) treatments is 26 patients (13 patients for each arms).

Since the study will be using both efficacy analysis, higher sample calculated using HOMA-IR was chosen as reference ie 26 subjects required for study.

Green et al (Vitamin D status and its association with parathyroid hormone concentrations in women of child-bearing age living in Jakarta and Kuala Lumpur)^15^ found 60% of population to have 25 (OH) Vit D of < 50nmol/L. Assuming a similar prevalence exist in our population, we thus expect to screen at least 44 women to recruit 26 subjects for the study.

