| **Statistical methods:**   1. Sample size and power considerations   By using nQuery Advisor version 6.01, from paper written by Von Hurst et al (Vitamin D supplementation reduces insulin resistance in South Asian women living in New Zealand who are insulin resistant and vitamin D deficient - a randomised, placebo-controlled trial )^31^, a sample size of 9 will have 95% power to detect a difference in means of 0.700 (e.g. the differences between Group 1 mean, µ1, of 0.800 and a Group 2 mean, µ2, of 0.100), assuming that the common standard deviation is 0.384, with a 0.050 two-sided significance level. By adding 40% dropped out patient in case of lost to follow up or unplanned pregnnacy, the total sample for 2 arms (placebo and treatment group) treatments is 26 patients (13 patients for each arms).  Green et al (Vitamin D status and its association with parathyroid hormone concentrations in women of child-bearing age living in Jakarta and Kuala Lumpur)^15^ found 60% of population to have 25 (OH) Vit D of < 50nmol/L. Assuming a similar prevalence exist in our population, we thus expect to screen at least 44 women to recruit 26 subjects for the study.  Green et al (Vitamin D status and its association with parathyroid hormone concentrations in women of child-bearing age living in Jakarta and Kuala Lumpur)^15^ found 60% of population to have 25 (OH) Vit D of < 50nmol/L. Assuming a similar prevalence exist in our population, we thus expect to screen at least 44 women to retain 26 subjects for the study. |

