## 10.2 Randomization

Subjects will be randomly allocated to either Vitamin D3 or Placebo in a 1:1 ratio. Once a patient meets the inclusion and exclusion criteria at the end of screening, she will be randomized through process of central independent randomization with help of CRC hospital Pulau Pinang.

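### The 40% dropout allowance is applied as 9 × 1.4 = 13 per arm instead of 9/0.6 = 15, so 26 women do not give 95% power, and another section claims a 50% allowance.

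*Protocol*

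**What the plan says.** The HOMA-IR calculation appears in the Synopsis (Statistical methods) and again in section 10.1. It states that "a sample size of 9 will have 95% power to detect a difference in means of 0.700", taken as "the differences between Group 1 mean, µ1, of 0.800 and a Group 2 mean, µ2, of 0.100", and "assuming that the common standard deviation is 0.384, with a 0.050 two-sided significance level". The allowance for loss follows: "By adding 40% dropped out patient in case of lost to follow up or unplanned pregnnacy, the total sample for 2 arms" is given as 26, with 13 in each arm. Section 10.1 names this calculation as the one that sets the trial's size.

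The section on dropouts and withdrawals, under Study Conduct, gives a different rate: "50% drop out rate is included in statistical calculation".

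Section 10.1 also sizes the trial on AUC insulin. It takes 4 subjects from a paired comparison (mean difference 4.610, standard deviation of differences 1.200), adds 40%, and concludes that the total for two arms "treatments is 11 patients".

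Section 10.3.1 defines a per-protocol analysis. Women not treated as intended, and those lacking efficacy data, are left out.

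**The concern.** A loss allowance should leave the required number of evaluable women after the loss has occurred. Multiplying by 1 + d does not do this, because the loss is taken from the larger, inflated number; the required number must be divided by 1 − d. The 13 per arm looks like the product of the first formula, so the 95% power would not survive the loss the protocol says it expects.

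The second loss rate makes this worse. If 50% is the real expectation, 26 women fall further short. If 40% is, the statement about 50% is wrong. A reader cannot tell what attrition the trial was built to withstand. Because the analysis is per protocol, women who drop out without efficacy data add nothing to power.

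**Working it through.** **Inputs (section 10.1 unless noted).** Difference δ = 0.700; common SD σ = 0.384; two-sided α = 0.05; 9 evaluable per arm (per arm, since 13 per arm follows from it); loss 40% in section 10.1 and the Synopsis, 50% under dropouts and withdrawals; 1:1 allocation (section 10.2).

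**1. Reproduce the base figure.** Two-sample t-test with noncentrality δ / [σ√(1/n₁ + 1/n₂)] on n₁ + n₂ − 2 degrees of freedom.

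- 9 per arm: 0.7 / (0.384 × √(2/9)) = 3.87 on 16 df, power 95.2%.
- 8 per arm: 0.7 / (0.384 × √(2/8)) = 3.65 on 14 df, power 92.3%.

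Nine per arm is therefore correct, and is the smallest number that reaches 95%.

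**2. Reproduce the inflated figure.**

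| Loss d | 9 × (1 + d) | 9 / (1 − d) | Completers from 13 |
|---|---|---|---|
| 40% | 12.6 → 13 per arm (26) | 15 per arm (30) | 13 × 0.6 = 7.8 |
| 50% | 13.5 → 14 per arm (28) | 18 per arm (36) | 13 × 0.5 = 6.5 |

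The stated 13 comes only from multiplying by 1.4. A 50% rate gives 14 or 18, never 13. The same section does divide when it sets the screening number: 26/0.60 = 43.3, giving 44.

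**3. Power that 26 women deliver.**

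- 40% loss: 26 × 0.6 = 15.6 completers. With 8 + 8, power is 92.3%; with 8 + 7, 90.2%.
- 50% loss: 26 × 0.5 = 13 completers. With 7 + 6, power is 84.6%.

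These assume a near-even split. If each woman is lost independently with the stated probability, power averaged over the possible outcomes is 89% at 40% and 81% at 50%. Somewhat heavier loss gives 87.8% (7 + 7) or 81.2% (6 + 6).

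**4. Loss that 13 per arm can absorb.** 1 − 9/13 = 4/13 = 30.8%, below both rates the protocol gives.

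**5. AUC insulin.** For a paired t-test with difference 4.61 and SD of differences 1.2, 4 subjects give 99.7% power and 3 give 89.0%, so 4 is the right minimum for that test. The total is 4 × 2 × 1.4 = 11.2, rounded down to 11, an odd total under 1:1 allocation. Dividing gives 8/0.6 = 13.3, or 14. In addition, an SD of within-subject differences powers a before-after change, whereas the trial's comparison is between vitamin D and placebo.

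**The case against.** The best defence is literal. The protocol attaches 95% power to 9 subjects, which is correct, and then says it adds 40%; 9 plus 40% is 12.6, so 13 is sound arithmetic. Nowhere does it say outright that 26 women with 40% lost still have 95% power. This does not hold up, because the text presents the addition as cover for dropped-out patients and the Study Conduct section calls it a drop-out rate. A reader will take 26 as the number that protects the stated power at that loss.

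A second defence is that withdrawn women are asked to complete final assessments (procedures for handling withdrawal), so some might still supply data. Section 10.3.1 largely closes this off, since it excludes women not treated as intended as well as those with missing efficacy data.

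Two points on scale do stand. Power stays above 80% at either rate under the protocol's inputs, and type I error and the endpoints are untouched. The AUC-insulin figure sets nothing, because section 10.1 takes the larger HOMA-IR number, so that part is secondary.

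**Conclusion.** The concern holds. The trial is four women short of the 30 that its own 95% power and 40% loss require, and ten short of the 36 that 50% loss requires. With 26 randomised, type II error rises from 5% to about 8% to 10% at 40% loss and about 15% at 50%, given a near-even split; under independent random loss it averages about 11% and 19%. The two loss rates contradict each other, and the claim that 50% is built into the calculation is false under either formula.

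These figures rest on the protocol's difference of 0.700 and SD of 0.384, a two-sample t-test, and an analysis confined to completers. The shortfall does not make the trial unviable, but the power and attrition allowance are wrong as written and should be corrected.

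**What to change.** 1. Choose one expected loss rate and use it in the Synopsis, section 10.1, and the section on dropouts and withdrawals.
2. Keep 26 women and replace the inflation sentence with one of these:
   - *Thirteen women will be randomised per arm. With 40% loss, about 15 to 16 of 26 complete, giving 90% to 92% power if losses are balanced between arms* (for a 50% rate: about 13 complete, power about 85%). It is worth adding that random loss lowers the average to about 89% (or 81%).
   - *Thirteen women per arm retain 95% power provided loss does not exceed 31%.*
3. Delete the AUC-insulin total of 11, or recalculate it for the between-arm comparison, dividing by 1 − d and rounding up to an even number.

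This is a wording change with no extra patients; its only cost is a less favourable power statement. If the sponsor would rather plan for 9 completers per arm at 40% loss, that means 30 women and, at the assumed 60% prevalence, screening 30/0.60 = 50 instead of 44.

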## 10.2 Randomization

Subjects will be randomly allocated to either Vitamin D3 or Placebo in a 1:1 ratio. Once a patient meets the inclusion and exclusion criteria at the end of screening, she will be randomized through process of central independent randomization with help of CRC hospital Pulau Pinang.

## 10.3 Analysis

### *10.3.1 Analysis Sets*

Analysis will be according to protocol. Two categories of subjects were excluded:

- - Subjects who failed to receive the treatment as intended
  - Subjects who have experienced protocol violation, including missing data on efficacy assessment.

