### *Procedures for handling withdrawal*

Subjects who withdraw or are withdrawn from the study should:

- Have the reason(s) for their withdrawal recorded
- Be asked about the presence of any AEs
- Be seen by an investigator and all final assessments will be performed and recorded
- Have study treatment returned.

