### *Adverse Events (AE)*

Vitamin D dietary supplementation may be detrimental in persons already receiving an adequate intake through diet and exposure to sunlight. Minimum of 2000iu of Vit D3 is the recommended replacement dose for patients with vitamin D deficiency. No adverse events are anticipated for this study using 4000iu Vit D3 or placebo in women with documented vitamin D insufficiency.

Excessive intake of vitamin D (50,000 iu daily for a few months) can lead to development of hyperphosphataemia or hypercalcaemia. Associated effects include hypercalciuria, ectopic calcification, renal and cardiovascular damage. Symptoms of overdosage include anorexia, lassitude, nausea and vomiting, constipation or diarrhoea, polyuria, nocturia, sweating, headache, thirst, somnolence and vertigo. Hypersensitivity reactions can occur.

(Source: Martindale : The complete drug reference)

The 8 weekly dispensing of study meds will allow for monitoring and reporting of any unforeseen adverse event. Subjects are instructed to contact via phone for earlier review in event of AE or intolerance to study meds. Patient with intolerance of vitamin D leading to poor compliance will be excluded from trial.

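### Section 10.3.1 makes a per-protocol set the only analysis of a randomised placebo comparison and drops women even where their outcomes have been recorded

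*Protocol*

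**What the plan says.** Section 10.3.1 of the protocol is the only text on analysis populations. It opens with "Analysis will be according to protocol. Two categories of subjects were excluded" and lists two groups. The first is "Subjects who failed to receive the treatment as intended". The second is "Subjects who have experienced protocol violation, including missing data on efficacy assessment". Violation is not defined and is not limited to major violations.

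Other sections bear on who reaches that set:

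- Procedures for handling withdrawal says that women who withdraw, or are withdrawn, should "Be seen by an investigator and all final assessments will be performed and recorded".
- Adverse Events (AE) says "Patient with intolerance of vitamin D leading to poor compliance will be excluded from trial".
- Treatment and follow up of AE and Criteria for stopping subject treatment withdraw women who become pregnant. The latter also allows discretionary withdrawal.
- The allowance for loss is given twice, differently. Section 10.1 and the Synopsis have "By adding 40% dropped out patient in case of lost to follow up or unplanned pregnnacy"; Dropouts and withdrawals has "50% drop out rate is included in statistical calculation".

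**The concern.** The primary objective is efficacy against placebo in a randomised, double-blind, parallel-group trial, planned around a two-sided test of a difference in means. Randomisation makes the two arms comparable as allocated. Adherence, violations and attendance are all determined afterwards and may be related to outcome. Restricting the only analysis to women who did well on those counts gives a comparison that randomisation no longer protects, and it answers the efficacy question only for adherent completers without violations.

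This is not a detail left open for a statistical analysis plan. The protocol itself chooses the population, and a plan that followed it would have to be per-protocol. The rule also sits awkwardly with the withdrawal procedure, which has outcomes recorded that section 10.3.1 then leaves out for women not treated as intended.

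**Working it through.** **1. The plan's own figure.** Inputs from section 10.1: difference 0.700, SD 0.384, two-sided alpha 0.05, and "a sample size of 9 will have 95% power to detect a difference in means of 0.700". For a two-sample t-test with 9 per arm, the noncentrality is 0.700 / (0.384 × √(2/9)) = 3.87 on 16 degrees of freedom, which gives 95.2% power. Then 9 × 1.40 = 12.6, rounded up to 13 per arm, 26 in total. The stated figure reproduces.

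**2. How many women the planned loss leaves.**

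| Loss allowance | Source | Left of 26 | Per arm | Power for 0.700 |
|---|---|---|---|---|
| 40% | Section 10.1, Synopsis | 15.6 | 7.8 | 0.90 (7 v 8) to 0.92 (8 v 8) |
| 50% | Dropouts and withdrawals | 13.0 | 6.5 | 0.85 (6 v 7) |

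The 40% is tied to loss to follow-up and unplanned pregnancy, and the 50% to drop-outs. Most of these women would lack a usable final outcome under any analysis set. The table describes attrition, not what section 10.3.1 costs. Exclusions for non-adherence or violation could add to it, but the protocol gives no rate for them.

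**3. Illustration of the bias from exclusion.** Assume no true effect. A fraction p of the vitamin D arm is excluded, and those women do worse than the retained women by δ standard deviations. Exclusion on placebo is unrelated to outcome. The retained vitamin D mean then differs from the full-arm mean by p × δ. Type I error is the rejection probability of a two-sided 5% t-test with 8 per arm at that shift; the noncentrality is shift / √(2/8).

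| p | δ (SD) | Shift (SD) | Shift (HOMA-IR, × 0.384) | Share of 0.700 | Type I error |
|---|---|---|---|---|---|
| 0.10 | 0.5 | 0.05 | 0.02 | 3% | 5.1% |
| 0.20 | 1.0 | 0.20 | 0.08 | 11% | 6.6% |
| 0.40 | 0.5 | 0.20 | 0.08 | 11% | 6.6% |
| 0.40 | 1.0 | 0.40 | 0.15 | 22% | 11.6% |
| equal p and δ in both arms | – | 0 | 0 | 0 | 5% |

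The values of p and δ, and the one-sided mechanism, are assumptions. None comes from the protocol.

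**4. Cost of including non-adherent women.** Assume that all 13 per arm attend and that untreated women have no effect. If 40% are untreated, the difference becomes 0.6 × 0.7 = 0.42 and power is about 76%. If 20% are untreated, it becomes 0.8 × 0.7 = 0.56 and power is about 95%.

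**The case against.** Four replies have force.

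- **The loss is mostly not caused by the analysis rule.** A woman lost to follow-up has no week-24 OGTT whatever the analysis set is called, and the protocol itself says pregnancy may alter glucose metabolism. This stands. A reader might infer that section 10.3.1 throws away 40% to 50% of the trial, but the documents do not support that. The two percentages are also conflicting planning allowances, not the ends of a stated range.
- **Asymmetry between arms is not established.** The intolerance clause names vitamin D, so a reader might infer that it removes women from the active arm only. Subjects and assessors are blinded, however, so intolerance can be judged only against the capsule, and the same section anticipates no adverse events on either treatment. Unequal exclusion is a risk, not something the protocol predicts.
- **The bias figures rest on a chosen scenario.** This also stands. Equal selection in both arms gives zero, and nothing in the documents shows that vitamin D would be favoured.
- **The retained women are still compared as allocated, and the withdrawal assessments need not be week-24 values.** Both are true. It would be too strong to say that the randomised comparison is discarded, or that every withdrawn woman has a usable endpoint.

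None of this justifies a per-protocol set as the only analysis. The rule still removes women whose outcomes exist, for reasons that arise after randomisation.

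**Conclusion.** The point holds as a defect in a stated rule. Section 10.3.1 fixes a sole per-protocol analysis for a superiority comparison, and nothing else in the protocol supplies an as-assigned analysis. The efficacy result is therefore open to selection bias of unknown size and direction.

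Under the one-sided assumptions above, type I error runs from about 5.1% to 11.6%. The upper end requires all of a 40% exclusion on vitamin D to be informative at a full standard deviation, with none informative on placebo. These figures show sensitivity and are not estimates for this trial. The point does not depend on the 40% or 50% allowance. It should be settled before the trial's efficacy claim rests on this analysis.

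**What to change.** Rewrite section 10.3.1 so that the primary analysis compares all randomised women by assigned arm, using every available outcome regardless of adherence or protocol violation. Add a sensitivity analysis for missing outcomes; its method can be left to the statistical analysis plan. Keep the per-protocol set as supportive, with violations defined.

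Reconcile Procedures for handling withdrawal, Adverse Events (AE), Treatment and follow up of AE, Criteria for stopping subject treatment and section 10.3.1 on which women leave treatment, follow-up or analysis. Poor compliance alone should not remove outcome data already collected. Pregnancy withdrawals stay as the protocol has them. Reconcile the 40% and 50% loss allowances.

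The cost is wording and a little more analysis, plus a possibly smaller estimate and lower power because non-adherent women are included (step 4 of the working). The change does not recover women who are truly lost to follow-up.
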